# RiMINI – the influence of rifaximin on minimal hepatic encephalopathy (MHE) and on the intestinal microbiome in patients with liver cirrhosis: study protocol for a randomized controlled trial

**DOI:** 10.1186/s13063-016-1205-8

**Published:** 2016-02-29

**Keywords:** Hepatic encephalopathy, Minimal hepatic encephalopathy, Liver cirrhosis, Rifaximin

## Abstract

**Background:**

Hepatic encephalopathy (HE) is a clinically significant complication of liver cirrhosis impacting on the patients’ quality of life. Minimal hepatic encephalopathy (MHE) is diagnosed by psychometric tests, found in up to 80 % of patients with liver cirrhosis and carries a high risk of progression to overt HE. Continuous therapy with rifaximin in combination with lactulose significantly reduces the risk of overt HE, recurrence of HE and HE-related hospitalizations in randomized, double-blind, placebo-controlled clinical trials. Rifaximin is approved for the therapy of overt HE in Germany. Treatment with lactulose has been shown to improve cognitive functions in patients with liver cirrhosis. Data from prospective clinical trials comparing the efficacy of rifaximin alone against a combination of rifaximin and lactulose in the treatment of MHE are scarce. Changes in the microbiome of the upper and lower gastrointestinal tract as a result of therapy with rifaximin have not yet been addressed in clinical studies.

**Methods and design:**

RiMINI is a monocentric exploratory pilot study on 60 patients with MHE as assessed by critical flicker frequency (CFF). Additionally, visual evoked potentials’ (VEP) testing, electroencephalography (EEG) and psychometric testing (NCT-A) will be carried out. Patients will be randomized to treatment either with rifaximin alone (550 mg twice daily (bid) continuously for a period of 3 months) or with rifaximin (550 mg bid continuously) in combination with lactulose (30–60 ml daily) for 3 months. An esophagogastroduodenoscopy (EGD) will be performed at baseline, at the end of treatment and 6 and 12 weeks after the end of treatment to obtain gastric and duodenal biopsies and aspirates. The samples will be analyzed for their content of specific bacterial taxae by applying next generation sequencing (NGS) after rRNA isolation to identify the microbiome of the stomach and duodenum, and of the gut, in patients with liver cirrhosis and MHE before and after therapy.

**Discussion:**

Differences of the effect of antibiotic therapy with rifaximin alone or in combination with lactulose on the clinical course of MHE are assessed.

**Trial registration:**

The trial was registered as DRKS00006359  on March 17th 2015, with the universal trial number U1111-1163-9410 and with EudraCT2013-004414-18.

## Background

Hepatic encephalopathy (HE) is defined as an unspecific brain function disorder, due to either failure of (cirrhotic) liver function or to port osystemic shunting and thus by-passing the functional parenchyma. For an accurate diagnosis of HE, other brain diseases have to be properly excluded. HE is characterized by cognitive, psychiatric and/or motoric impairment [1] leading to changes in the circadian rhythm, atmospheric fluctuations, phased loss of concentration, increased forgetfulness, irritability, and somnolence up to hepatic coma [2]. Subclinical neurological deficits are defined as minimal hepatic encephalopathy (MHE). The presence and degree of (M)HE can only measured by psychometric tests and clinically apparent deficits, graded by the West Haven criteria [1, 3]. Clinically apparent (i.e., overt) HE is estimated to be present in 30–45 % of patients with liver cirrhosis and leads to frequent hospitalization, impairment of health-related quality of life (HRQL) and ability to work [4]. Up to 80 % of cirrhotic patients present with MHE with cognitive dysfunction in special diagnostic testing [5, 6, 7]. In patients with MHE activities of daily life are affected resulting, among other problems, in an increased risk for accidents when driving and navigating [8]. The clinical manifestations of HE in each stage are potentially reversible by adequate therapeutic management. MHE is currently under-diagnosed in patients with liver cirrhosis and carries a high potential for progression to overt HE. Current therapies are directed at the reduction of ammonia production from the gastrointestinal tract by administration of the non-absorbable disaccharide lactulose and the non-absorbable antibiotic rifaximin [9–18].

### Rationale for the explorative study

Continuous therapy with rifaximin in combination with lactulose significantly reduces the risk of overt HE, recurrence and HE-related hospitalization in randomized double-blind placebo-controlled clinical trials [1–3]. Rifaximin is approved for the therapy of *overt* HE in Germany. Therapy with lactulose has been shown to improve cognitive functions in patients with liver cirrhosis. So far, whether monotherapy with rifaximin is as effective as combination therapy with rifaximin and lactulose in the treatment of MHE, has not been addressed in a prospective clinical trial.

Rifaximin is a minimally absorbed gut-selective antibiotic and thus impacts on the intestinal microbiome. The role of the intestinal microbiome in the pathophysiology of HE is still little understood. To our knowledge, changes in the microbiome of the upper gastrointestinal (GI) tract as result of therapy with rifaximin have not yet been addressed in clinical studies and studies addressing the persistence of changes of the intestinal microbiome are scarce [19].

## Methods and design

RiMINI is a monocentric exploratory pilot study on 60 patients with MHE as assessed by critical flicker frequency (CFF) analysis. Additionally, visual evoked potentials’ (VEP) testing, electroencephalography (EEG) and a psychometric test (NCT-A) will be carried out. The patients will be randomized to treatment either with rifaximin alone 550 mg twice daily (bid) continuously for a period of 3 months or to continuous treatment with 550 mg rifaximin bid in combination with lactulose 30–60 ml daily (to pass 2–3 semisoft stools/day) for 3 months. An esophagogastroduodenoscopy (EGD) will be performed at baseline, at the end of antibiotic treatment, as well as 6 and 12 weeks after the end of treatment to obtain gastric and duodenal biopsies and aspirates will be taken. The samples will be analyzed for their specific bacterial taxae by applying next generation sequencing (NGS) after ribonucleic acid (RNA) isolation. Additionally, stool samples will be taken at the same time points. Prevalence of *Helicobacter pylori*, which is the predominant gastric microbe, will be assessed by histology, rapid urease test and serology at study entry. For clinical assessment, quantification of MHE and therapeutic effects, CFF, EEG, VEP and psychometric tests are assessed weekly during the first month and every 4 weeks from the beginning of the second month until the end of the post-treatment follow-up.

Changes in the gut microbiome from antibiotic therapy with rifaximin alone or rifaximin with lactulose are analyzed comparing pre- and post-antibiotic time points. The follow-up data will show whether the change in the gut microbiome is persistent or transient. We will compare the effect of antibiotic therapy with rifaximin alone with a combination therapy with lactulose on the clinical course of MHE. As planned, NGS methods (Illumina sequencing, Illumina, San Diego, CA, USA) will be used to characterize the composition and changes of both stomach and small bowel microbiomes. Bacterial ribosomal ribonucleic acid (rRNA) will be isolated from aspirates, biopsies and feces and then stored in RNAlater at −80 °C. The samples will be analyzed by NGS methods as described below with the aim of identifying the microbiome of the stomach and the small bowel, as well as of the large bowel, in patients with liver cirrhosis and MHE and its changes before and after therapy (Fig. 1).

**Fig. 1 Fig1:**
[figure not shown]
Study flow chart

### Methods for studying intestinal microbiota

Samples will be taken following a strict algorithm. Aspirates will be collected using a sterile, straight endoscopic retrograde cholangiography (ERC)-catheter via a standard gastroscope (Olympus 180). After collecting the aspirate from the duodenum (pars descendens), biopsies will be taken from this area after removal of the catheter. Afterwards gastric juice will be aspirated using a second sterile catheter. Biopsies will be taken from the antral region of the stomach for RNA extraction. Additional biopsies for histopathological examination, rapid urease testing and culturing of *H. pylori*, if infected, will be taken from the duodenum, the gastric antrum, the angulus and the gastric corpus. After completion of the endoscopic procedure, a saliva sample will be taken directly from the oral cavity of the patients. All samples determined for RNA extraction will be stored directly in 1 ml RNAlater (Sigma-Aldrich, St. Louis, MO, USA) and kept at room temperature for at least 4 hours (maximum 8 hours). Afterwards, samples will be stored at −80 °C. RNA will be extracted from the aspirates, feces and biopsies using the RNeasy Mini Kit following the manufacturer’s instructions (Qiagen, Hilden, Germany). In summary: the biopsies will be relocated from the RNAlater into buffer solution as specified, whereas the liquids will be centrifuged for 10 minutes at 15,000 rpm and 4 °C and resuspended into buffer solution. The solutions will be replaced in Lysing Matrix E tubes and the cells will be lysed and homogenized using a Fast Prep™-24 instrument (MP Biomedicas, Solon, OH, USA) for 2 × 45 seconds, interrupted by a 1-minute ice cooling break. Additionally, we will complement a second digestion of deoxyribonucleic acid (DNA) on the columns using the RNase-Free DNase Set (Quiagen, Hilden, Germany) working with 70 μl RDD buffer and 10 μl DNase for each sample for 8 minutes. Finally, the RNA will be eluted in 32 μl RNase-free water.

To synthesize first-strand complementary deoxyribonucleic acid (cDNA) the SuperScript® III First-Strand Synthesis System (Invitrogen™, Carlsbad, CA, USA) will be used following the manufacturer’s instructions.

The V1–V2 region of the 16S rRNA gene will be amplified using primers based on 27F and 338R primers. The primers include sequences complementary to the Illumina-specific adaptors to the 5′ends that are used in the course. Amplification will be performed in a total volume of 50 μl with 5x PrimeSTAR TM buffer (Clontech Laboratories, Mountain View, CA, USA). Each deoxyncleoside triphosphate will be contained at a concentration of 2.5 mM and each primer will be contained at a concentration of 0.2 μM. One microliter of cDNA template will be used with 0.5 μl PrimeSTAR TM HS DNA polymerase (2.5 U, Clontech Laboratories, Mountain View, CA, USA). The polymerase chain reaction (PCR) will be started with an initial denaturation step of 95 °C for 3 minutes, followed by 15 cycles of denaturation at 98 °C for 10 seconds, annealing at 55 °C for 10 seconds and extension at 72 °C for 45 seconds. Non-template control (water) and positive control (*Staphylococcus aureus* DSM3463) were used to exclude contaminants and systematic errors. A second PCR will be performed using 1 μl reaction product under the same conditions for 20 cycles using PCR primers designed to integrate the sequence of the specific Illumina multiplexing sequencing primers and index primers. Negative control (water) will document the absence of contaminants.

Following the third PCR amplicons will be verified by agarose gel electrophoresis and purified using Macherey-Nagel 96-well plate purification kits (Macherey-Nagel, Düren, Germany) following the manufacturer’s instructions. The products will be quantified with the Quant-iT PicoGreen double-stranded deoxyribonucleic acid dsDNA) reagent and the associated kit (Invitrogen, Darmstadt, Germany).

Amplicon libraries will be prepared by pooling equimolar ratios of amplicons (200 ng/sample). After combining five libraries with unique barcode primers and different index primers, a second precipitation step will be performed to remove any contaminants. The supernatant will be removed, air dried and resuspended in 30 μl of double-distilled water. The product will be separated on a 2 % agarose gel. PCR products of the correct size will be extracted and recovered using the QIAquick gel extraction kit (Qiagen, Hilden, Germany). Libraries will be sent for 150-nt paired-end sequencing on a GAIIX Genome Analyzer (Illumina, San Diego, CA, USA).

The sequencing analyses will be followed by bioformatical analyses using Primer7 (Primer-E Ltd, Lutton, United Kingdom).

### Primary objective

This study primarily aims at the analysis of the efficacy of MHE therapy with rifaximin alone or in combination with lactulose on the improvement of neuropsychometric and neurophysiological changes.

### Secondary objective

Composition and changes in the composition of the intestinal microbiome of the upper GI tract, as well as of the large bowel, before, during and after therapy of MHE with either a combination of lactulose and rifaximin or rifaximin monotherapy are the focus of further analyses.

### Eligibility/Description

Patients of either sex are eligible for this trial provided they meet all inclusion and exclusion criteria.

### Inclusion criteria

Individuals who are suitable to participate as determined by the outcome of medical history, physical assessment, and clinical judgment of the investigator can be included into the study.

In order to participate in this study, all subjects must meet all the following inclusion criteria in the “All subjects” section below.

### All subjects

Men and women in the age range 18–90 years at the time of enrollment and who are mentally competent, willing and able to understand the nature and risks of the proposed study, and able to sign the consent form prior to study entry. The individuals must have a projected life expectancy of 6 months or longer and must be able to comply with all study procedures and requirements. Women with childbearing potential must have a negative pregnancy test during the screening period. The diagnosis of liver cirrhosis is needed, established either by histology or by typical signs on transabdominal ultrasound in combination with signs of portal hypertension (ascites, enlarged spleen, fundic or esophageal varices), and the presence of MHE has to be confirmed. To confirm the diagnosis of MHE the following tests will be performed: number-connection test A (NCT-A), critical flicker frequency analysis (CFF), electroencephalography (EEG), and visual evoked potentials (VEP) whereby the final confirmation of MHE depends on the CFF result (CFF <39 Hz). The additional neurophysiological and neuropsychometric tests will be analyzed concerning diagnostic utility alone or in combination.

### Exclusion criteria

Individuals with any of the following medical conditions are excluded from participation in the trial:

Any documented underlying allergic condition against rifaximin or lactulose, underlying blindness *or* eye axis deviation *or* red-green color blindness. The presence of overt HE rules out participation in the study. Antibiotic treatment within 28 days before study entry or during the study constitutes an exclusion criterion. Individuals who are not sufficiently healthy as determined by medical history, physical assessment, and clinical judgment of the investigator are excluded. Individuals who are unable to follow the required study procedures for the whole period of the study and/or who have behavioral or cognitive impairment or psychiatric disease that, in the opinion of the investigator, may interfere with the subject’s ability to participate in the trial, are excluded. Individuals who are expected to be hospitalized (except for endoscopic therapy of esophageal varices) or undergo surgery during the study period or who have participated in another clinical study within 30 days prior to enrollment into the study are not allowed to participate. Individuals with ongoing drug or alcohol abuse that, in the opinion of the investigator, would interfere with the subjects’ safety or the evaluation of the study objectives, and individuals who are member of the research staff or have relatives who are member of the research staff, are excluded. Women with childbearing potential who have a positive pregnancy test (positive urine or serological (beta HCG)), and pregnant or lactating women are not allowed to participate as are women who are unwilling to use an acceptable method of birth control up to visit 4. Acceptable methods of birth control include (1) established use of oral, injected or implanted hormonal methods of contraception: placement of an intrauterine device or intrauterine system, (2) barrier methods of contraception: condom or occlusive cap (diaphragm or cervical/vault caps) with spermicidal foam/gel/film/cream/suppository, (3) male sterilization (with the appropriate post-vasectomy documentation of the absence of sperm in the ejaculate), (4) true abstinence from heterosexual sexual intercourse: when this is in line with the preferred and usual lifestyle of the subject. (Periodic abstinence (e.g., calendar, ovulation, symptothermal, post-ovulation methods) and withdrawal are not acceptable methods of contraception). Individuals with a medical history of any illness that may, in the opinion of the investigator, pose additional risk to the subject due to participation in the study, are also excluded.

### Prior and concomitant medication

Patients may receive concomitant therapy during the study as required. Any concomitant medication at baseline as well as any changes made in concomitant medication within the study period (until the last follow-up examination) will be recorded in the electronic Case Report Form (eCRF). All concomitant therapy will be recorded using generic names. The necessity to use antibiotic therapy besides rifaximin leads to exclusion from this study.

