### Withdrawal and replacement criteria for treatment

Every patient has the right to refuse further participation in the study at any time and without providing any reasons. A patient’s participation will be terminated immediately upon their request. The investigator should seek to obtain the reason and record this in the eCRF. This study is designed as an intention-to-treat (ITT) study.

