### Statistical analysis

All demographic and baseline variables are presented in descriptive statistics stratified by treatment arm in the full analysis set (FAS, all randomized patients). Exploratory tests, according to the level of the respective variables, will search for differences between both arms which might occur despite randomization. The primary target variable is compared between both treatment arms. The odds ratio for treatment success is calculated between both treatment arms together with the corresponding two-sided 95 % confidence interval. If the confidence interval is completely above or below the threshold of 1, the superiority of the corresponding treatment arm with larger success rates can be concluded. If the confidence interval covers the threshold of 1, then the lower and upper confidence limits give limits which can be used in non-inferiority statements. This analysis is performed primarily in the modified full analysis set (MFAS, all randomized patients but excluding those with missing CFF tests) according to the ITT principle. Missing values are imputed by the last observation carried forward principle.

Secondary analyses for the primary target variable include (1) logistic regression analysis with treatment arm, sex, age and baseline value of CFF as co-variables, (2) analog analyses in the per protocol set (PPS, patients of the MFAS excluding those with severe protocol violations), (3) analog analyses for the result of CFF at end of follow-up, (4) description of the results of the psychometric tests (mean and standard deviation) per treatment arm and comparison in two-sample *t* tests (both at end of treatment and end of follow-up).

The secondary efficacy variables are compared between the treatment arms in analysis of covariance (ANCOVA) models with treatment arm, sex, age and respective baseline variable as factors or co-variables, respectively.

Safety analysis is done in the safety set (SS, patients receiving at least one treatment) in descriptive and exploratory analyses. Laboratory variables and rates of SAEs are compared between both treatment arms using the Mann-Whitney *U* test and Fisher’s exact test.

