## Discussion

Rifaximin treatment for patients with overt HE has been shown to be effective in the amelioration of cognitive function and in the prevention of recurrence of overt HE [14]. In patients with MHE rifaximin significantly improves cognitive function and HRQL [13, 14]. However, more than 90 % of patients with HE treated in prospective studies received a combination therapy of rifaximin and lactulose. Only a single prospective trial with a limited number of subjects addressed the effect of rifaximin on MHE [13]. The primary objective of our study, therefore, is to analyze the efficacy of rifaximin alone or in combination with lactulose on the improvement of neuropsychometric and neurophysiological changes in patients with MHE. Although current therapeutic concepts in the treatment of HE are directed to reduce bacterial ammonia production by antibiotic treatment, the role and contribution of the upper-GI microbiota in the pathogenesis of HE remain poorly understood. The secondary objective of this study aims at evaluating the microbial diversity and the composition of the microbiota in the upper GI tract, and in the stool, in cirrhotic patients with and without MHE before, during, and after therapy to assess the degree of changes and whether they are transient or persistent.

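### Randomized patients who need a non-study antibiotic are excluded from the study, which conflicts with the stated ITT design and leaves their later CFF outcome unobserved

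*Protocol article*

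**What the plan says.** Two sections of the protocol article state the antibiotic rule. Exclusion criteria: "Antibiotic treatment within 28 days before study entry or during the study constitutes an exclusion criterion". Prior and concomitant medication: "The necessity to use antibiotic therapy besides rifaximin leads to exclusion from this study". Both arms receive rifaximin as study treatment, so the second sentence describes patients already in the trial.

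Two sections state the analysis principle. Withdrawal and replacement criteria for treatment: "This study is designed as an intention-to-treat (ITT) study". Statistical analysis places the primary odds ratio in the "modified full analysis set (MFAS, all randomized patients but excluding those with missing CFF tests) according to the ITT principle", and adds: "Missing values are imputed by the last observation carried forward principle". The same section defines a full analysis set of all randomized patients, used for baseline description, and a per-protocol set (PPS) that removes severe protocol violators from the modified full analysis set (MFAS).

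None of these set definitions mentions antibiotic use. No section says whether a patient excluded under the antibiotic rule continues to attend CFF assessments.

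**The concern.** An eligibility criterion belongs before randomization. Here, part of the criterion can be met only afterwards, and the stated consequence is exclusion from the study. An intention-to-treat comparison needs the outcome of each randomized patient whatever happens after allocation, so the two statements cannot both be followed as written.

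The event is unlikely to be neutral. A patient with cirrhosis who needs an antibiotic usually has an infection. The article's Discussion also says that "current therapeutic concepts in the treatment of HE are directed to reduce bacterial ammonia production by antibiotic treatment", so a further antibiotic could itself move CFF. The article gives no data on either link; plausibly related to outcome is as far as one can go.

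At stake is the end-of-treatment CFF behind the primary comparison, and the end-of-follow-up CFF used in a secondary analysis of the same variable. A CFF value that is never measured cannot be recovered by any later analysis plan.

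**Working it through.** The article gives no antibiotic rate, success rate, dropout rate or power figure, so there is no stated number to reproduce. The check has two parts.

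**1. What happens to an excluded patient.** Table 1 schedules the neurocognitive tests at screening, weekly to day 28, then every 4 weeks, at end of treatment, and 6 and 12 weeks later. Suppose a patient is excluded partway through treatment and has no CFF afterwards. The Statistical analysis section leaves two routes:

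- *Route A:* the patient counts as having missing CFF tests and leaves the MFAS.
- *Route B:* the last CFF before exclusion is carried forward and the patient stays in the MFAS.

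Route A removes a randomized patient because of a later event. Route B keeps the patient but scores a value from before that event. For an exclusion after end of treatment, Route B would let an earlier, possibly on-treatment, value stand for the end-of-follow-up result. Under both routes the actual outcome is unobserved.

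**2. What this can do to the odds ratio.** From the article: 60 patients, 1:1, so about 30 per arm. Assumed: 15 successes in each arm, so the true odds ratio (OR) is (15/15)/(15/15) = 1.00. The Woolf interval is exp(ln OR ± 1.96 × SE), with SE = √(1/a + 1/b + 1/c + 1/d). Removing x failures from one arm and y from the other gives OR = [15/(15 − x)] / [15/(15 − y)].

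| Failures deleted (x vs y) | OR | 95% CI |
|---|---|---|
| 0 vs 0 | 1.00 | 0.36 to 2.75 |
| 3 vs 3 | 1.00 | 0.34 to 2.93 |
| 3 vs 0 | 1.25 | 0.44 to 3.55 |
| 6 vs 3 | 1.33 | 0.43 to 4.10 |
| 6 vs 2 | (15/9)/(15/13) = 1.44 | 0.48 to 4.39 |
| 6 vs 0 | 1.67 | 0.56 to 4.97 |

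For 6 vs 2, SE = √(1/15 + 1/9 + 1/15 + 1/13) = 0.567.

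If the same eight patients are instead carried forward as failures (Route B), the table stays at 15/30 vs 15/30 and the OR is 1.00.

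*A milder case under Route A.* Let 50% succeed in each arm, a fraction e be excluded, and 20% of the excluded be successes. The remaining success rate is (0.5 − 0.2e)/(1 − e).

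- e = 0.20: 0.46/0.80 = 0.575
- e = 0.10: 0.48/0.90 = 0.533
- e = 0.05: 0.49/0.95 = 0.516

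The OR is (0.575/0.425)/(0.533/0.467) = 1.18 for 20% vs 10%, and 1.27 for 20% vs 5%. If the excluded succeed at the same 50%, or if exclusion is equal in the two arms, the OR stays 1.00.

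*Precision under Route A.* With an assumed 10% to 20% excluded, 6 to 12 of 60 patients are lost. The log-OR interval widens by 1/√0.9 = 1.054 to 1/√0.8 = 1.118, about 5% to 12%.

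*Route B is not always harmless.* The 1.00 above holds because the patients were assumed to be true failures. If 3 of the 6 and 1 of the 2 would have succeeded but carry forward a failure, the counts are 12/30 vs 14/30 and the OR is (12/18)/(14/16) = 0.76.

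**The case against.** The best defence is that exclusion may mean only that participation ends, while the data already collected are analysed by intention to treat. No analysis set names antibiotic use. If the MFAS dropped everyone with any missing CFF, the carry-forward rule would have little left to do, so a coherent reading is that it keeps patients who have a usable earlier value. With CFF measured weekly in the first month, most excluded patients would have one. This stands in part: a reader should not infer that all such patients disappear from the primary analysis. It does not answer the point, because their outcome after the event is still not measured.

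Three further inferences are tempting and not supported:

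- *That the rule serves only the microbiome objective.* The article gives no reason for it, and its Discussion ties antibiotic effect to HE treatment itself, so protecting the CFF comparison is an equally possible motive.
- *That safety information on infections is lost.* Safety assessment requires all adverse events in the eCRF, and medication changes are recorded too. The triggering event is captured; at most its later course is missed.
- *That the primary comparison is biased.* That needs exclusion, or its relation to outcome, to differ by arm. The open-label design makes this possible, since need is judged with the arm known, but nothing in the article shows it.

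It can also be said that this is an exploratory pilot, and that handling of data after withdrawal often sits in the full protocol or analysis plan. That lowers the severity. It does not remove the conflict, because the article states the exclusion outright and a later plan cannot supply unmeasured CFF values.

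**Conclusion.** The point holds as a conflict between the antibiotic rule and the intention-to-treat statements, with the consequence that end-of-treatment or end-of-follow-up CFF goes unobserved after a post-randomization event plausibly related to outcome. That CFF stops being collected is the natural reading of exclusion from the study, not an express statement.

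The size cannot be fixed from the article. Under the assumed 15/30 successes per arm, the OR moves from 1.00 to 1.44 if 6 versus 2 failures are deleted, and stays at 1.00 if they are carried forward as failures or if exclusions are balanced under equal rates. All the shifts shown are small beside the confidence intervals of a 60-patient trial. Should be fixed, with moderate confidence.

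**What to change.** Reconcile Exclusion criteria, Prior and concomitant medication, Withdrawal and replacement criteria, and Statistical analysis along these lines:

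- Only antibiotic use before study entry is an eligibility criterion.
- Randomized patients who later receive a non-study antibiotic remain in the scheduled CFF assessments, as far as they consent, and in the primary analysis of all randomized patients. The antibiotic is recorded as an intercurrent event.
- These patients are left out only of the PPS, and their samples taken after the antibiotic are left out of the microbiome analysis.

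This concerns follow-up and analysis sets only. It does not bear on clinical care or on whether study treatment continues.

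The cost is an amendment to the wording and CFF visits already in the schedule. The same visits also carry repeat endoscopies in Table 1, so the amendment should say that the request is for CFF. The downside is that the primary estimate then includes some patients with extra antibiotic exposure; the PPS, already planned, addresses this as a sensitivity analysis. Recruitment is under way, and CFF values missed under the present rule cannot be obtained later.
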